### Annual community-based parasitological surveys

#### Selection of houses and participants

For the annual community-based surveys, 70 housing structures per shehia will be selected by a computer-based randomisation procedure from Geographical Information System (GIS) shape files provided by the Zanzibar Mapping Initiative (http://www.zanzibarmapping.com) of the Commission of Lands Zanzibar. Randomly selected housing structures will be located by field enumerators by using the navigation app Maps.me (https://www.maps.me/) combined with ODK installed on a computer tablet (Samsung Galaxy Tab A 2019). Accounting for a 30% dropout of housing structures that may not be inhabited (i.e. shops, sheds, mosques, houses under construction or abandoned houses) and households without any member willing to participate, we estimate that we will have a final sample size of 50 houses per shehia included in the survey. People sharing the same kitchen or pot will define a household. All household members meeting the inclusion criteria will be invited to participate in the survey and to provide one own urine sample, which will be examined for *S. haematobium* infection markers. With an average of five people per household, we estimate to collect urine samples from a total of 250 participants per shehia. Additionally, one adult household member present at the first visit to the house will be invited to participate in a questionnaire survey to assess household characteristics. If more than one adult is present and eligible to participate at first visit, we will randomly select the participant of the questionnaire survey by using a playing-cards approach.

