### School-based parasitological surveys

#### Selection of participants

The annual school-based cross sectional survey will be conducted in the main public primary school of each shehia. If a shehia has several public primary schools, the school with most students will be surveyed. If a shehia has no public primary school, no school will be surveyed. In each of the schools, a total of 175 students aged 4–17 years will be randomly selected for urine collection. For this purpose, one class of each nursery and standard 1–6 grades, will be selected based on computer-randomised lists. In the selected classes, all children will line up, stratified by sex. Subsequently, we will systematically select each third child in the lines to be included in the study until 25 children per class are reached. This procedure will be continued until we reach a total of 175 selected children from the 7 selected grades. Accounting for a 20% drop-out due to non-consenting parents, absenteeism of children or inability to produce a urine sample of sufficient volume, we aim for a final sample size of 20 children per standard (i.e. a total of 140 students per school).

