#### Intervention packages and data collection in hotspot implementation units

In the hotspot IUs, where a considerable part of the population is still infected with *S. haematobium*, we will implement a multi-disciplinary intervention package including MDA, snail control and behaviour change communication activities.

Large-scale MDA with praziquantel is the corner stone for the control and prevention of morbidity due to schistosomiasis [3, 5]. Praziquantel treatment is administered without prior diagnosis to large parts of the population living in endemic areas. In our hotspot IUs, MDA will be conducted at least annually in communities and schools by the Zanzibar NTD Programme. In communities, community drug distributors trained by the MoHSWEGC will visit all households in a door-to-door approach and offer to treat children aged 4 years or older with praziquantel (40 mg/kg) if they do not receive treatment in schools. Moreover, they will offer praziquantel to all adults that are eligible for treatment according to national treatment guidelines. In schools, praziquantel (40 mg/kg) will be provided to all children present at the day of treatment by teachers and staff of the Zanzibar NTD Programme using a dose pole [50]. The intake of tablets will be directly observed. Treatment coverage will be reported by the Zanzibar MoHSWEGC based on reports from their staff, community drug distributors, and teachers. Moreover, we will conduct our own post-treatment coverage surveys in line with the annual cross-sectional parasitology surveys in the hotspot communities and schools. When invited to submit a urine sample for annual monitoring, individuals enrolled in the survey will also be invited to respond to an ODK questionnaire, asking if they have received and swallowed the drugs provided in the MDA treatment round preceding the survey.

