### Sample size

We run a series of simulations to assess how precisely the sensitivity of the surveillance system can be estimated. We modelled different scenarios with varying prevalences in schoolchildren as well as in the general population, different values for clustering and different assumptions for diagnostic test accuracy and surveillance system performance. The results revealed that sampling an average of 140 schoolchildren and 250 community members in each of 15 low-prevalence shehias in the cross-sectional surveys enables us to estimate the prevalence with a median precision (defined as one half length of the confidence interval) of 10 to 15 percentage-points in schoolchildren and of 5 to 7 percentage-points in the general population. The bias (defined as difference between the sensitivity calculated using the apparent prevalence observed during cross-sectional surveys and the sensitivity calculated using the "true" apparent prevalence observed during the surveillance activities) had a median of zero and an interquartile range from − 0.05 to 0.05.

Hence, conducting the cross-sectional surveys in the schools and communities of all 20 study shehias, the yearly total sample is 7800 individuals (ca. 10% of the population, based on an average of 4000 inhabitants per shehia).

In addition, during the surveillance activities in 15 low-prevalence shehias, we roughly estimate to test annually about 12,150 individuals (ca. 20% of the population). Among them, around 7500 will be subjected to active surveillance in high-risk schools (estimated n = 15 shehias*1 school*450 children + estimated n = 15 shehias*1 school*50 children = 7500 samples per year), 750 to reactive surveillance in households (estimated n = 15 shehias*10 households*5 inhabitants = 750 samples per year) and 1500 at mobile test-and-treat stalls (estimated n = 15 shehias*10 water bodies *10 people = 1500 per year), and 2400 to passive surveillance in health facilities (estimated n = 20 health facilities*12 months*10 patients = 2400 samples per year).

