### Statistical methods

To analyse the primary outcome, we define the sensitivity of the surveillance system as the proportion of cases detected:$${\text{SE}} = {\text{N}}_{{{\text{inf detected by surveillance}}}} / {\text{N}}_{{{\text{inf}}}}$$

The total number of infected persons is unknown but will be estimated from the cross-sectional surveys as:$${\text{N}}_{{{\text{inf}}}} = {\text{ P}}_{{{\text{school}}}} *{\text{ N}}_{{{\text{school}}}} + {\text{ P}}_{{{\text{non}} - {\text{school}}}} *{\text{ N}}_{{ {\text{non}} - {\text{school}}}}$$whereby prevalences (P) and corresponding confidence intervals are estimated via generalized estimating equations for binary data with independent correlation structure to account for correlation within clusters.

The prevalence and intensity of *S. haematobium* infections will be calculated by different diagnostic approaches used in the annual cross-sectional surveys. Intensity of infection will be classified into light (< 50 eggs/10 ml urine) and heavy (≥ 50 eggs/10 ml urine) according to thresholds provided by the WHO for urine filtration results [3].

The timeliness of case notification and reactive intervention will be assessed by recording the time needed from diagnosis to treatment, from diagnosis to follow-up of *S. haematobium* positive individuals and test-and-treat of their household members, and from diagnosis to reactive snail control.

The acceptability of the surveillance-response approach will be assessed by a mixed methods approach based on the results of questionnaires run in parallel to test-and-treat approaches in low-prevalence shehias.

The coverage of test-and-treat activities will be calculated by assessing the number of people who were targeted by test-and-treat activities in relation to the total population.

MDA coverage will be calculated by assessing the number of people reporting in the cross-sectional surveys that they received praziquantel during the last MDA in relation to the total number of participants in the cross-sectional surveys.

MDA compliance in hotspot areas will be calculated by assessing the number of people reporting in the cross-sectional surveys that they have taken praziquantel as recommended, in relation to the total number of participants in the cross-sectional surveys.

The impact of snail control will be determined by assessing the snail abundance and number of intermediate host snails at each HWCS identified over time during regular snail surveys.

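### Taken literally, the MDA coverage and compliance ratio pools a household sample with an extra pupil sample and so does not estimate coverage of the shehia population

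*Protocol article*

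**What the plan says.** The rule stands in the protocol article, Statistical methods. Coverage is the number of people who report that they "received praziquantel during the last MDA in relation to the total number of participants in the cross-sectional surveys". Compliance in hotspot areas is the number who report that "they have taken praziquantel as recommended, in relation to the total number of participants in the cross-sectional surveys". Neither definition names a survey, a stratum or a weight.

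Other sections show what those surveys contain:

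- **Two components.** The section on annual cross-sectional parasitological surveys places them in all 20 communities and in their main public primary schools. The hotspot section confirms that both feed the coverage data: "we will conduct our own post-treatment coverage surveys in line with the annual cross-sectional parasitology surveys in the hotspot communities and schools".
- **Community sample.** "All household members meeting the inclusion criteria will be invited to participate in the survey", with eligibility from age 4, and "we estimate to collect urine samples from a total of 250 participants per shehia". School-going children are therefore already included.
- **School sample.** After drop-out the target is "a total of 140 students per school". A shehia without a public primary school has no school survey.
- **Sizes.** The Sample size section works with "sampling an average of 140 schoolchildren and 250 community members in each of 15 low-prevalence shehias" and gives a yearly total of 7,800 for 20 shehias.

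For the primary outcome, the same Statistical methods section separates school from non-school and multiplies each prevalence by the size of its group.

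**The concern.** The household sample represents residents aged 4 or older in roughly their natural proportions. The school sample is an additional draw from one subgroup. Dividing by the sum of the two gives pupils more weight than they have in the shehia, so the result is not the coverage of any defined population.

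This matters where pupils and other residents differ in uptake. The hotspot section describes two delivery channels: distribution in schools to the children present, and a door-to-door offer to eligible adults and to children aged 4 or older who are not treated in school. Equal coverage cannot be presumed.

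MDA coverage in hotspot areas is a named secondary outcome, and the Discussion calls good coverage key to success. A mis-weighted figure could conceal a difference between the two groups. It would also mean different things in hotspot shehias with and without a surveyed school.

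**Working it through.** **Reproducing the plan's figures.** School: 7 grades × 25 = 175, and 175 × 0.8 = 140. Community: 50 houses × 5 people = 250. Yearly total: 20 × (140 + 250) = 7,800, as stated. The article's own total thus treats both samples as the cross-sectional surveys.

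**Pupil share in the pool.** Let s be the share of pupils among residents. The article does not state s, so it is an assumption. The pooled share is (140 + 250s)/390. The school sample alone contributes 140/390 = 35.9%.

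| s | pooled pupil share | ratio to s |
|---|---|---|
| 0.20 | 48.7% | 2.44 |
| 0.25 | 51.9% | 2.08 |
| 0.30 | 55.1% | 1.84 |
| 0.40 | 61.5% | 1.54 |

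**A value of s from the article.** The Sample size section uses 450 children per main school for active surveillance, and the surveillance section says that grades 3–5 are registered. With equal grade sizes, 450/3 × 7 = 1,050 children from nursery to grade 6. Then 1,050/4,000 = 26.25%, the pooled share is (140 + 65.6)/390 = 52.7%, and the ratio is 2.01. Counting six grades gives 900/4,000 = 22.5%, a pooled share of 50.3% and a ratio of 2.24.

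**Bias in the ratio.** With coverage c₁ in pupils and c₀ in others, pooled minus population coverage is (140/390) × (1 − s) × (c₁ − c₀). At s = 0.2625 the multiplier is 0.359 × 0.7375 = 0.265. The gaps below are assumed, because the article gives none:

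- gap +10 points: +2.6 points
- gap +20 points: +5.3 points
- gap +30 points: +7.9 points
- no gap: 0
- gap −10 points: −2.6 points

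For a 20-point gap, the bias runs from 5.7 points (s = 0.20) to 4.3 points (s = 0.40). Example with 90% in pupils and 70% in others: the population value is 0.2625 × 90 + 0.7375 × 70 = 75.2%, and the pooled value is 0.527 × 90 + 0.473 × 70 = 80.5%.

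**Shehias without a school survey.** There the same formula uses the community sample alone and the bias term disappears. Two shehias with identical coverage by group could therefore report different figures.

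**Who answers.** The data collection section of the community survey puts the MDA question to one adult per household. The hotspot section has the enrolled individuals answer. If one adult in each of 50 households answers only for themselves, the pool is 140 pupils to 50 adults, or 140/190 = 73.7% pupils.

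**The case against.** The strongest reply is that pooling is inferred. The definitions speak of surveys in the plural, and the article otherwise keeps the two apart, with separate sampling, separate data collection and separate prevalence thresholds. One coverage figure per survey is a possible reading, and survey source and age are recorded, so stratified figures could still be produced. This supports treating the point as a correction of wording. It does not remove it: the stated denominator is a single total, and the same section shows that the authors separate and weight the groups when they intend to. Because a formula is stated, this is also more than detail left to a fuller document.

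A reader might infer that reported coverage will be overstated. The article does not support that. It gives no coverage by group, so the size and sign of the error are conditional.

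A reader might also take the delivery contrast too far. The door-to-door offer is not confined to adults, since it extends to children aged 4 or older not treated in school. The statement that intake is observed follows the sentence on schools but is not expressly limited to them. What stands is that the channels differ.

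Finally, this is a descriptive secondary outcome, and the Ministry reports programme coverage separately. Both are true and limit the weight of the point.

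**Conclusion.** The point holds for the rule as written. In shehias with a surveyed school, pupils receive about 1.5 to 2.4 times their population weight for assumed shares of 20–40%, and about twice on the share derived from the article with equal grades. The mis-weighting follows from the sample sizes alone. A biased coverage figure follows only if uptake differs between groups: about 2.6 points for each 10-point gap at a 26% share, in either direction. Compliance has the same denominator and the same fault. The sensitivity of the surveillance approach, the primary outcome, is not affected. The point should be corrected but does not threaten the study's main result.

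**What to change.** In Statistical methods, state that population MDA coverage and compliance in hotspot shehias are estimated from the community survey, and report the school-survey figure separately. If one combined figure is wanted, weight the pupil and non-pupil estimates by their shares of the shehia population, as the section already does for the primary outcome.

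At the same time, reconcile the community data collection section (one adult per household answers on MDA) with the hotspot section (enrolled individuals answer). The community estimate and its precision depend on this.

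The text change is one or two sentences. The price of the community-only estimate is a wider interval. If all enrolled individuals answer, it rests on about 250 instead of 390 people per shehia. Under simple random sampling and ignoring clustering, that widens the interval by a factor of √(390/250) = 1.25. If only one adult per household answers for themselves, it rests on about 50 adults and says nothing about children. In that case the question would have to be put to all enrolled household members for the fix to work.

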### Laboratory procedures and data collection

The urine samples that are collected in the study will be examined with the following techniques for *S. haematobium* infections at the PoC, or in the laboratories of PHL-IdC, located in Chake Chake, Pemba.

In the annual cross-sectional parasitological surveys and for active, reactive and passive surveillance, urine samples will be screened for microhaematuria using reagent strips (Haemastix; *Siemens* Healthcare Diagnostics AG; Zürich, Switzerland). The colorimetric test results will be recorded semi-quantitatively (0 = negative, 1 =  + , 2 =  +  + , 3 =  +  +  + , 4 = trace).

Additionally, in the cross-sectional parasitological surveys and from a subset of samples collected during active and reactive surveillance, urine samples will be examined for the presence and number of *S. haematobium* eggs using the urine filtration method. For this purpose, urine samples will be shaken vigorously and 10 ml of each sample will be filtered through a filter-holder containing a 13 mm polycarbonate filter (Sefar, Bury, United Kingdom), using a plastic syringe [59]. All *S. haematobium* eggs present on the filter will be counted under a microscope by experienced laboratory technicians and exact egg counts will be recorded for each participant.

For external quality control, all microscope slides with the filter containing potential *S. haematobium* eggs collected during the annual cross-sectional surveys will be covered with cellophane soaked in glycerol and stored in slide storing boxes at PHL-IdC in Pemba until the end of the survey period. After each survey period, 10% of the slides will be selected based on the original electronic results by a Swiss TPH epidemiologist, sorted out locally and re-read by an external senior laboratory technician who is blinded to the results. The number of *S. haematobium* eggs counted in quality control will be recorded and compared with the original results as part of the statistical analysis done at Swiss TPH. In the case of significant discrepancies (false negatives, false positives, egg counts resulting in a different infection intensity category) in more than 20% of the re-read slides, all stored slides of the last survey will be re-read.

Both, reagent strip and urine filtration methods are not very sensitively detecting light intensity infections, as they might occur frequently in people living in elimination settings such as Pemba [29]. Hence, 10 ml from each urine samples collected at the baseline and endline survey will be stored at -20 °C and examined with a highly sensitive and specific test at the end of the study. This might be a DNA-based PCR approach [31] or an antigen-based test such as the up-converting phosphor-lateral flow circulating anodic antigen (UCP-LF) CAA assay [30] or any other test with excellent parameters developed until 2024.

To increase the performance of our surveillance-response approach, ideally a PoC test with a higher sensitivity and specificity than the reagent strips will be used. No such tests are yet (in 2021) commercially available, but several are under development. In the SchistoBreak project, we will investigate the performance of new rapid diagnostic tests, such as the Recombinase Polymerase Amplification (RPA) assay [44, 60], or other DNA-based, antigen-based or egg-based diagnostic tests for *S. haematobium* diagnosis at the PoC during our cross-sectional and surveillance activities. Once validated, applicable at the PoC, and available and affordable in sufficient numbers to screen our participants, promising candidates might be applied throughout the cross-sectional surveys and surveillance activities of the SchistoBreak project.

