### Interventions and data collection

In the study, specific intervention packages will be tailored and adapted to the local micro-epidemiology of urogenital schistosomiasis in the shehias. Low-prevalence IUs will receive tailored surveillance-response measures, consisting of active, passive and reactive case finding, treatment of *S. haematobium*-positive individuals and focal snail control. Hotspot IUs will receive a multi-disciplinary intervention package including MDA, snail control and behaviour change communication. The classification of the study shehias into low-prevalence or hotspot IUs will be based on the results of annual cross-section surveys. Initially, a shehia will be considered a low-prevalence IU if it shows an apparent *S. haematobium* prevalence < 2% in the community-based survey and an apparent *S. haematobium* prevalence < 3% in the school-based survey, based on single urine filtration microscopy. Otherwise, the shehia will be considered a “hotspot” IU (Fig. 3). Results gained over the study period will show whether these thresholds and respective intervention packages successfully sustain and accelerate the gains and prevent recrudescence of *S. haematobium* transmission in low-prevalence IUs. The thresholds will be evaluated annually in light of the results of the cross-sectional surveys and adapted if needed.

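### The slide re-read trigger counts discrepancies over all re-read slides, so at an assumed 1–3% prevalence it cannot detect a reader who misses half of the positives

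*Protocol article*

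**What the plan says.** Under Laboratory procedures and data collection, all cross-sectional slides are stored, and after each survey "10% of the slides will be selected based on the original electronic results by a Swiss TPH epidemiologist". A blinded external technician re-reads them. The events that count are "significant discrepancies (false negatives, false positives, egg counts resulting in a different infection intensity category". If they occur "in more than 20% of the re-read slides, all stored slides of the last survey will be re-read". The denominator is therefore every re-read slide. No separate limit is set for recorded positives or recorded negatives, and the mix of the two in the 10% is not given. The same section says that the quality-control counts are compared with the original ones in the statistical analysis.

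Under Sample size, "the yearly total sample is 7800 individuals", from 140 schoolchildren and 250 community members per shehia.

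Under Interventions and data collection, a shehia counts as low-prevalence with "prevalence < 2% in the community-based survey" and "prevalence < 3% in the school-based survey, based on single urine filtration microscopy". The Discussion expects very few infected people.

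**The concern.** When nearly all slides are truly negative, a discrepancy rate over all re-read slides is dominated by easy agreements. The error to fear in an elimination setting is the missed light infection. Its contribution to that rate under random selection cannot exceed the prevalence itself, which lies far below 20%. A limit that looks strict may then tolerate a reader who overlooks most of the infections.

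The annual classification is what is at stake. By the cut-offs in Interventions and data collection, 5 positives of 250 in the community, or 5 of 140 in the school, make a shehia a hotspot. The Discussion gives the two cut-offs the other way round, which would mean 8 of 250 and 3 of 140; the two sections must be reconciled. On either version a few slides decide which intervention package a shehia receives.

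**Working it through.** **Inputs.** From the protocol: 20 shehias, 140 + 250 samples each, 10% re-read, limit above 20%. Assumed, because the protocol gives no figure: a true egg-positive prevalence of 1–3%, consistent with the classification cut-offs and the expectation of very few infected, and a reader who misses half of the positives and makes no other error.

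**The plan's own figure.** 20 × (140 + 250) = 7,800, as stated.

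**The trigger.** 10% × 7,800 = 780 slides; 20% × 780 = 156; more than 156 means at least 157 discrepant slides.

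**Half of the positives missed.** T = true positives = 7,800 × prevalence; missed M = T/2; recorded positives R = T − M.
- Random selection: expected discrepant = 780 × M / 7,800.
- All recorded positives plus random recorded negatives: (780 − R) × M / (7,800 − R).
- Upper bound, every missed slide re-read: M / 780.

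| True prevalence | T | M | Random | All recorded positives included | Upper bound |
|---|---|---|---|---|---|
| 1% | 78 | 39 | 3.9 (0.5%) | 3.7 (0.5%) | 5% |
| 2% | 156 | 78 | 7.8 (1.0%) | 7.1 (0.9%) | 10% |
| 3% | 234 | 117 | 11.7 (1.5%) | 10.1 (1.3%) | 15% |

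Fewer than 157 missed slides exist in the whole survey in every row, so missed positives alone cannot fire the rule under any choice of 780 slides.

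**Sensitivity to the assumed prevalence.** Put 15 shehias at their cut-offs (15 × (250 × 0.02 + 140 × 0.03) = 138 positives) and five hotspots at 5%, 10% or 20% (97.5, 195 or 390 positives). Overall prevalence is 3.0%, 4.3% or 6.8%, and half missed gives 1.5%, 2.1% or 3.4% discrepant under random selection. The expected rate reaches 20% only when half the prevalence is 20%, that is, at a true prevalence of about 40%.

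**Errors among recorded positives.** Suppose all recorded positives are re-read. At 1% or 2% recorded prevalence there are 78 or 156 of them, so the rule cannot fire on these slides even if every one is wrong. At 3% there are 234, and 157/234 = 67% must be wrong.

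**Effect on classification (illustration, simple binomial without clustering).** A community with 4% true prevalence and 250 samples falls below the 2% cut-off with at most 4 recorded positives. The probability is 3% with correct reading, and 44% when half are missed (recorded positivity 2%).

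**The case against.** 1. **The sample may be enriched.** The slides are chosen from the original results, so recorded positives may be over-represented. That can expose false positives or wrong intensity classes. It does not find missed positives, which lie among the recorded negatives; the table shows the discrepancy rate falling slightly with full enrichment.

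2. **Under-reading would not be invisible.** A reader might infer that nothing would reveal it. The protocol does not support that. The re-read counts are compared with the originals, every survey sample also has a reagent strip, baseline and endline urine is to be retested with a highly sensitive test, and the Discussion admits that cases will be missed. This stands. But none of these is tied to an action on the slides, and the retest comes at the end of the study, too late for annual classification.

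3. **The primary outcome may be unaffected.** A reader might also infer that the surveillance sensitivity will be inflated. Statistical methods does not name the test that supplies the prevalences in N_inf. If reagent strips supply numerator and denominator, slide reading does not enter. If the same filtration readers supply both, equal under-reading largely cancels. Only if filtration supplies the prevalences while surveillance cases come mainly from strips would halved prevalences halve N_inf and double the estimate. The effect is conditional.

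4. **Laboratory detail belongs in an SOP.** True for the sampling mix. But the article states the fraction, the events, the limit, the denominator and the consequence, and those stated choices are what fail.

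**Conclusion.** The point holds for the stated trigger. At an assumed 1–3% true prevalence, missing half of the positives gives about 0.5–1.5% discrepant slides under random selection and at most 5–15% under any selection, against a limit of 20%. The conclusion does not hinge on the exact prevalence, since under random selection it reverses only near 40%.

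It would go too far to say that the rule can never fire. With enrichment and more than 2% recorded prevalence, a very high share of false-positive or misgraded slides could fire it. What it cannot do is its main job here, detecting gross under-reading. The established consequence is for shehia classification; a bias in the primary sensitivity follows only under the condition given above. The correction is worth making because it is cheap and the present rule gives false reassurance.

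**What to change.** Keep the 780 slides and the same re-reader, and replace the single trigger by two.

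- **Recorded positives.** Re-read all of them, or a stated fraction if they are numerous. If more than 20% are discordant in status or intensity class, re-read all stored slides.
- **Recorded negatives.** Fill the remainder with negatives drawn at random, stratified by shehia. Extrapolate the false-negative rate to all recorded negatives. If it implies that more than a stated share of positives (for example 20%) was missed, re-read all stored negatives.

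At 2% prevalence, 20% missed is 31 of 156, leaving 125 recorded positives, 7,675 recorded negatives and 780 − 125 = 655 re-read negatives. The expected finding is 655 × 31 / 7,675 = 2.6, so the limit is about 3 or more. Hypergeometric probabilities that it fires:

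| Positives missed | 5% | 10% | 20% | 30% | 50% |
|---|---|---|---|---|---|
| 3 or more | 0.02 | 0.14 | 0.50 | 0.79 | 0.98 |

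A limit of 4 fires with probability 0.04 at 10% missed and 0.93 at 50% missed.

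The cost is a change of wording, no added routine reading, and sometimes a re-read of some 7,700 negatives for a reader within tolerance. The choice between 3 and 4 should be made with these error rates in view. The sponsor should also state which test supplies the prevalences in N_inf and reconcile the two versions of the classification cut-offs.
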